## Abstract

**Introduction:** Anal fistula is one of the commonest ailments seen by anorectal surgeons as surgery is currently the preferred treatment for it. Diabetes mellitus is a risk factor that can lead to slow wound healing after anal fistula surgery. Because of the large postoperative wound surface of anal fistula, patients with diabetes can have an increased probability of wound infection, which makes it hard to heal. There is an extensive clinical experience for wound healing in traditional Chinese medicine (TCM). The Jiedu Shengji decoction (JSD) is a widely used external washing decoction in clinical practice. However, the current evidence on it is still insufficient. Therefore, we report this carefully designed clinical trial to assess the efficacy and safety of JSD in the treatment of postoperative wounds in diabetic patients with anal fistula.

**Methods and analysis:** This study was designed to be a randomized, double-blind, placebo-controlled, multi-center clinical trial. There were 60 eligible participants who were randomized at a 1:1 ratio to the intervention and placebo groups. Both groups received the same standard treatment. The intervention group was given external washing decoction of TCM (JSD), while the placebo group was given the placebo made of excipients and flavoring agents. The main outcome measures include wound healing, distribution of wound pathogens, levels of inflammatory mediators, and blood glucose. The secondary outcome measures included lipids, the quality of the life evaluation scale (Short-Form Health Survey 36). Assessments were performed before the start of the study, at 1st, 2nd, 3rd, and 4th weeks after the intervention, and at 8th, 12th, and 16th follow-up weeks.

**Discussion:** The clinical study we proposed will be the first randomized, double-blind, placebo-controlled, multi-center clinical trial study to assess the efficacy and safety of TCM external washing (JSD) in the treatment of postoperative wounds in diabetic patients with anal fistula.

**Ethics and dissemination:** The Medical Ethics Committee of Hospital of Chengdu University of Traditional Chinese Medicine has reviewed this study protocol and gave its approval and consent on 17 March, 2022 (Ethical Review Number: 2022KL-018).

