Both groups received standard treatments, including health knowledge education regarding diabetes and anal fistula, formulations of recipes, and taking hypoglycemic, antihypertensive, hypolipidemic, and anti-infective drugs. A personalized treatment plan was formulated after consultation with an endocrinologist, and the plan was evaluated and adjusted throughout the process. The wound surface was routinely cleaned with povidone-iodine after daily defecation. The intervention group was given TCM external washing decoction, JSD (Figure 2), and the information of its constituent botanical drugs is shown in Table 1. The JSD decoction was prepared by the Department of Pharmacy, Hospital of Chengdu University of Traditional Chinese Medicine. The specific steps are as follows: (1) Bai Zhi, Zi Cao, and Dang Gui are added to 500 ml of water and soaked for 30 min, and the mixture of water and herbs is transferred to the decoction machine, boiled at high heat to 100°C under standard atmospheric pressure (the boiling time to 100°C should not be more than 5 min), turned to low heat and maintained the temperature constant at 85°C–95°C, then continued to decoct for 30 min, obtained 200 ml of the botanical drug liquid was filtered, and set aside. (2) A measure of 500 ml of water is added again, boiled to 100°C on high heat (boiling time to 100°C should not be more than 5min), turned down the heat and maintained the temperature constant at 85°C–95°C, and decocted for 45 min. (3) The liquid from the previous two steps are mixed to obtain a total of 400 ml of the liquid (liquid 1). (4) Grind Ru Xiang, Mo Yao, and Er Cha, in advance, are filtered through a 2-mm sieve, 400 ml of water is added, boiled in high heat to 100°C (boiling time to 100°C should not be longer than 5 min), turned down the heat and maintained the temperature constant at 85°C–95°C, added pre-ground Xue Jie and Bing Pian (filtered through 2 mm sieve) at the 14th min, continued to boil for 2 min to get 200 ml of the liquid (liquid 2). (5) Liquid 1 and liquid 2 are mixed thoroughly to get 600 ml of liquid. (6) After waiting for its temperature to 35°C–40°C, 200-ml herbal medicine bags are plasticized. The decoction was produced in the same batch as far as possible and quality-checked by the manufacturer. To ensure that the decoction is not contaminated, the decoction vessels and filtration and dispensing equipment were completely cleaned in advance to make sure there were no residuals.

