### 2.12 Primary outcomes

#### 2.12.1 Wound healing

Assessments were at T0, T1, T2, T3, and T4. At the same time, weekly assessments were conducted during weeks 1–4 of intervention.1) Wound healing rate: The wound area on the first postoperative day was the original area. The maximum length and width of the wound were measured with the calculated area. Formula: Wound healing rate = (original area-current area)/original area × 100%.2) Wound healing time: From the start of the dressing change to the complete epithelialization and healing of the wound.3) Wound secretion score (Table 2) (Gould et al., 2021): Wound with abundant secretion, two or more pieces of penetrated gauze, dressing change more than twice a day, 3 points; wound with much secretion, one piece of penetrated gauze, dressing change twice a day, 2 points; wound with little secretion, no penetrated gauze, 1 point; and wound with smooth surface and no obvious secretion, 0 point.4) Wound edema score (Table 2) (Gould et al., 2021): Wound with severe edema which is significantly more than the wound edge, surgical resection needed, 3 points; wound with obvious edema which is more than the wound edge, need dressing change to remit, 2 points; wound with mild edema, 1 point; and wound with no edema, 0 point.5) Granulation tissue color score (Table 2) (Gould et al., 2021): Bright red, 1 point; light red, 2 points; and purple, 3 points.6) Anal function evaluation: The Wexner incontinence score was used to evaluate the anal function of participants after wound healing (Zhang et al., 2020a), including the ability of the anus to control the intestinal fluid, bowel gas, and loose and formed stools.7) Anal pain score: The pain index tested before the dressing change on the first postoperative day was the baseline pain. The pain index after the first postoperative day was tested within 2 h after the dressing change. Pain values were tested using the visual analogue scale (Anal pain visual analogue scale, VAS) (Bondi et al., 2017).

**TABLE 2 T2:** Scale for assessing wound healing.

Wound secretion score (Gould et al., 2021)	Score
Would with smooth surface and no obvious secretion	0
Would with little secretion and no penetrated gauze	1
Wound with much secretion, one piece of penetrated gauze, and dressing change twice a day	2
Wound with abundant secretion, two or more pieces of penetrated gauze, and dressing change more than twice a day	3
Wound edema score (Gould et al., 2021)	Score
Wound with no edema	0

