#### 2.12.2 Distribution of pathogens on wound

Wound samples of participants were collected for pathogen isolation and cultured to perform identification on the automatic pathogenic microorganism identification instrument (Mark Biotechnology, United States). Weekly assessments were conducted during weeks 1–4 of intervention.

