#### 2.12.3 Levels of inflammatory mediators

ELISA was used to measure the levels of IL-6 and TNF-α in related tissues of wound drainage collected from the participants. The streptavidin-peroxidase (S-P) method was used to perform immunohistochemical staining on wound edge tissue samples, which were observed under a 400-fold light microscope and semiquantitatively measured using a medical image analysis system. Weekly assessments were conducted during weeks 1–4 of intervention.

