#### 2.12.4 Blood glucose

Blood glucose was measured four times per day by using a glucometer, including fasting and 2-h postprandial blood glucose of breakfast, lunch, and dinner.

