### 2.16 Sample size

According to the sample size estimation method for the comparison of two sample means, we preset the sample size of the placebo group and the intervention group for them to be equal. The calculation formula is as follows:
$$n=2\sigma^{2}\times \frac{f\left(\alpha ,\beta \right)}{{\left(\mu_{1}-\mu_{2}\right)}^{2}},$$

where *n* represents the overall sample size of the study, μ1 and μ2 are the mean values of the control group and the test group, respectively, and σ is the standard deviation. We set that the probability of making type I error in this study shall not be greater than 5%, and the probability of making type II error at the same time shall not be greater than 10%, that is, α = 0.05 and β = 0.1. Referring to Chinese literature reports on TCM external washing for the treatment of postoperative wound of anal fistula, the wound healing rate (%) in literatures was set as the clinical efficacy observation, the mean value was 33.35, and the standard deviation was 2.29 in the intervention group, and the mean value was 27.33 and the standard deviation was 2.67 in the placebo group. The estimated loss of the follow-up rate was 20%, so the total study sample size was 60, of which 30 was for the intervention group and 30 was for the placebo group.

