### 2.20 Data analysis

All data analyses were conducted by SPSS 24.0 software. Student’s t-test was performed on continuous normally distributed variables, the Wilcoxon rank-sum test on non-normal variables, and Pearson’s χ^2^ test on categorical variables. Data were presented as the mean ± standard deviation for continuous variables or percentage values for categorical variables. The statistical significance level was set at *p* < 0.05, and all the statistical tests were two-sided.

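### Section 2.12 declares 11 to 12 unranked primary variables, but the 5% type I error and the sample size in 2.16 relate to wound healing rate alone

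*Protocol article*

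**What the plan says.** The abstract states: "The main outcome measures include wound healing, distribution of wound pathogens, levels of inflammatory mediators, and blood glucose". It leaves lipids and the SF-36 as secondary. Section 2.12 repeats that division and fills in the primary domains:

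- **2.12.1 Wound healing:** seven numbered items, namely healing rate, healing time, secretion score, edema score, granulation color score, Wexner score and pain ("7) Anal pain score: The pain index tested before the dressing change on the first postoperative day was the baseline pain").
- **2.12.2 Pathogens:** "Wound samples of participants were collected for pathogen isolation and cultured", weekly in weeks 1 to 4.
- **2.12.3 Inflammatory mediators:** "ELISA was used to measure the levels of IL-6 and TNF-α in related tissues of wound drainage collected from the participants", together with semiquantitative immunohistochemistry on wound-edge tissue, weekly in weeks 1 to 4.
- **2.12.4 Blood glucose:** "Blood glucose was measured four times per day by using a glucometer", with no analysis visit given.

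No variable is ranked above another. Section 2.11 labels T1, four weeks after the final treatment, as the primary endpoint, and gives T2 to T4 lower or other labels.

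Section 2.16 sets α = 0.05 and β = 0.1 for a comparison of two means, where "the wound healing rate (%) in literatures was set as the clinical efficacy observation". In section 2.20, "The statistical significance level was set at" p < 0.05 and all tests are two-sided. The hypothesis in the Introduction is only that outcomes will be more positive with the decoction than with placebo.

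**The concern.** A 5% type I error belongs to one test, or to a set of tests that share it. Here it is justified for one variable, while the label of primary outcome is given to many. Nothing in the article says which primary result, or how many of them, would make the trial positive. A report could therefore present any primary variable that crosses p < 0.05 as success on a primary outcome while citing an error rate planned for wound healing rate alone. What is at stake is what the trial can claim: a nominal p < 0.05 on, say, granulation color would have the same standing as one on healing rate.

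**Working it through.** **The plan's own figures.** The plan states no error rate for the primary set. Its only error figure is α = 0.05, which is right for a single two-sided test. Its only sample size input is healing rate: means 33.35 and 27.33, SDs 2.29 and 2.67. With difference 6.02, pooled SD √((2.29² + 2.67²)/2) = 2.487 and f(α,β) = (1.960 + 1.282)² = 10.51, the formula in 2.16 gives 2 × 2.487² × 10.51 / 6.02² = 3.6. That is 4 per arm, 5 after 20% loss, and 10 in total, not 60. This mismatch is a separate matter and does not affect the present point. What matters here is that no other primary variable enters the calculation.

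**Count of primary variables (2.12.1 to 2.12.4).** Wound items 7, pathogens 1, IL-6 and TNF-α 2, blood glucose 1: 7 + 1 + 2 + 1 = 11. If the immunohistochemistry readout is a separate variable, the count is 12. Section 2.12.3 names no analyte for it, so both counts are carried.

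**Formulas.** One test per variable, one visit, each at two-sided 0.05, success on any one, no true effect:

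- Independent tests: 1 − 0.95^k. For example, 1 − 0.95^11 = 0.431 and 1 − 0.95^12 = 0.460.
- Common correlation ρ, with c = 1.960: 1 − ∫ φ(u) [Φ((c − √ρ·u)/√(1−ρ)) − Φ((−c − √ρ·u)/√(1−ρ))]^k du, by numerical integration.

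The documents give no correlations, so every ρ below is an assumption.

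| Tests | ρ = 0 | ρ = 0.3 | ρ = 0.5 | ρ = 0.7 | ρ = 0.9 |
|---|---|---|---|---|---|
| 4 (one per domain) | 18.5% | 17.4% | 15.6% | 13.0% | 9.4% |
| 11 variables | 43.1% | 37.5% | 30.4% | 22.3% | 13.1% |
| 12 variables | 46.0% | 39.7% | 31.9% | 23.2% | 13.5% |

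For 12 variables, the ratio to 5% runs from 13.5/5 = 2.7 to 46.0/5 = 9.2. With one variable at one visit the rate is 5%.

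**Does the T1 label resolve it?** The table already assumes one visit, so the label lowers none of these figures. Nor does it fit every primary: pathogens and mediators are listed only for weeks 1 to 4 of intervention, whereas T1 in 2.11 falls four weeks after the final treatment. Glucose has no listed visit.

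**The case against.** The strongest reply is that this is a condensed article. Multiplicity procedures are commonly left to the full protocol or SAP, and section 2.16 already shows which variable leads. The first part stands for the method of adjustment: its absence is not counted here. It does not cover the list itself. Which outcomes are primary is fixed in the abstract and in 2.12, and a SAP that chose one would contradict them.

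Second, the any-one-wins rule is not in the document. That is right. If every primary had to succeed, type I error would not rise. But no such rule is stated either, and the power calculation covers one variable only.

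Third, independence is implausible for seven measures of one wound. That stands too, so 43 to 46% is the upper end of the range and not the expected value.

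Three stronger readings are tempting, and the documents do not support them:

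- **Every primary is tested at up to eight visits.** Weeks 1 to 4 plus T1 to T4 give eight post-baseline assessments only for the repeated wound scores, and the abstract's schedule gives seven. Pathogens and mediators have four, healing time is one value per patient, and the Wexner score is taken after healing. Section 2.20 does not say that each visit is tested, and 2.11 ranks the visits.
- **There are at least 12 primary variables.** The immunohistochemistry may be a second assay of the same mediators, so 11 is possible.
- **Blood glucose adds a special error because treatment is adjusted.** Section 2.8 says of background care in both groups that "the plan was evaluated and adjusted throughout the process". That would tend to dilute a difference between arms; it does not inflate type I error. Glucose counts here only as one more unranked primary.

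**Conclusion.** The point holds in this form: the 5% in section 2.16 is an error rate for wound healing rate, not for the set of outcomes that section 2.12 calls primary. The true rate for that set is about 2.6 to 9 times 5% when counted by variable. Counted by domain, it is 18.5% under independence and still 9.4% at a correlation of 0.9. These sizes rest on three assumptions: success on any one primary counts, each variable is tested once at a single visit, and the correlations are as assumed. The direction of the conclusion does not depend on the correlation chosen or on whether the count is 11 or 12. No claim is made about testing at repeated visits.

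**What to change.** Name wound healing rate, the variable behind section 2.16, at T1 as the single primary outcome, tested at two-sided 5%. First reconcile when T1 falls: section 2.11 puts it four weeks after the final treatment, while the abstract lists weeks 1 to 4 after the intervention and then follow-up weeks 8, 12 and 16. Move the other six wound measures, pathogens, mediators and blood glucose to secondary, either Holm-adjusted or labelled nominal. Treat the other visits as supportive.

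Choosing healing rate over healing time is a judgement, since the Discussion stresses shortening healing time. Healing rate is preferred because it is the only variable with a planned error rate and power.

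The cost is more than wording. Section 3.1 has recruitment running from June to December 2022, so the change needs a justified amendment with ethics approval, as section 3.2 provides, made before unblinding. Data collection and the planned 60 participants are unaffected. The downside is that fewer outcomes can be claimed as primary.

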## 1 Introduction

Anal fistula is one of the commonest ailments seen by anorectal surgeons. The prevalence of fistula-in-ano is 12.3 cases per 100,000 population in men and 5.6 cases per 100,000 population in women (Mei et al., 2019). Patients with anal fistula usually present with a recurrent abscess or a draining fistula with various severities of symptoms and require surgical interventions (Pigot, 2015; Lu et al., 2019). At present, the preferred treatment on anal fistula is surgery, which is a way to completely cure it, with an unequivocal efficacy and low recurrence rate (Shi et al., 2021). However, the large postoperative wound surface, which can lead to a high probability of wound infection and long healing time, is the reason which causes physical and psychological fear in patients (Kochhar et al., 2014; Farag et al., 2019).

According to the 10th edition of the International Diabetes Federation Diabetes Atlas, it is estimated that the global diabetes prevalence is 10.5% (536.6 million people) in population aged from 20 to 79 in 2021, and this number will rise to 12.2% (783.2 million) in 2045 (Sun et al., 2022). Perianorectal abscess can easily happen on patients with diabetes due to their reduced skin resistance, which might develop into anal fistula. In addition, the high blood glucose level of diabetic patients can provide a favorable nutritional environment for bacteria to grow, which can easily cause postoperative wound infection or even necrosis to slow down wound healing. Studies have shown that diabetes is a risk factor leading to slow wound healing after anal fistula surgery (Wang et al., 2014; Mei et al., 2019; Wang et al., 2021).

Traditional Chinese medicine can exert great clinical effects on wound healing (Mosavat et al., 2015; Yan et al., 2020). In particular, TCM external washing has a long history, extensive experience, and positive efficacy in promoting wound healing after anal fistula surgery and has been commonly used for postoperative treatment in China. In traditional Chinese medicine, it is believed that dampness, heat, and static blood are the pathological characteristics of postoperative wounds in diabetic patients with anal fistula.

The Jiedu Shengji decoction (JSD) is a widely used external washing decoction in clinical practice, which has the functions of removing toxins for detumescence, discharging pus, and promoting granulation. The main botanical herbs in JSD are Zi Cao (*Arnebia euchroma* (Royle) Johnst.), Dang Gui (*Angelica sinensis* (Oliv.) Diels.), Ru Xiang (*Boswellia carterii* Birdw.), Mo Yao (*Commiphora myrrha* (T.Nees) Engl.), Xue Jie (*Daemonorops draco* (Willd.) Blume), Bing Pian (*Cinnamomum camphora* (L.) J.Presl), Bai Zhi (*Angelica dahurica* (Hoffm.) Benth. Et] Hook. f. ex Franch. et Sav), and Er Cha (*Acacia catechu* (L. F.) Willd). Preliminary studies have found that JSD can significantly reduce wound edema after anal fistula surgery, reduce nerve sensitivity, ease the pain in patients, and promote wound healing. However, this study was limited by its single-center and non-double-blind design. Therefore, a multi-center, double-blind, randomized, controlled clinical trial is needed to further determine the efficacy and safety of JSD in the treatment of postoperative wounds in diabetic patients with anal fistula. We proposed that patients treated with JSD will have more positive clinical outcomes than those with placebos.

## 2 Methods/design

### 2.1 Trial design

This study incorporates a randomized, double-blind, placebo-controlled, multi-center clinical trial and was developed according to the Standard Protocol Items: Recommendations for Interventional Trials (SPIRIT) statement (the SPIRIT checklist is shown in Supplementary Material S1). Every eligible participant was assigned either to the intervention group or the placebo group randomly. All patients received standard treatment. The detailed workflow is shown in Figure 1. The trial is supported by the science and technology planning project of Sichuan Province [grant no. 2021YFS0275]. The funders have no vote in the study design, data collection and analysis, manuscript preparation, or decision to publish.

**FIGURE 1 F1:**
[figure not shown]
Study process: flowchart of the study procedure.

### 2.2 Study population

Patients were recruited from three hospitals: the Affiliated Hospital of Chengdu University of Traditional Chinese Medicine, Yanjiang District Hospital of Traditional Chinese Medicine in Ziyang City, and Chengdu Anorectal Specialized Hospital.

### 2.3 Recruitment of participants

Three members (ZX, YL, and [name]) were involved in recruiting participants, and the other two members (SP and LL) were responsible for assigning participants to groups. Patients who met the study criteria and volunteered to participate in the study were asked to sign a written informed consent form (Supplementary Material S2) with a clear understanding of the purpose, procedures, and all potential risks associated with the study. Participants’ personal information was kept confidential, and only authorized researchers will have access to them. All paper forms pertaining to this study were kept in a locked and secure office. Participants may obtain dataset from respective authors upon reasonable request.

### 2.4 Patient and public involvement

Patients or the public were not involved in the design, conduct, reporting, or dissemination plans of our research.

### 2.5 Inclusion criteria

1. Confirmed diabetes mellitus (Alberti and Zimmet, 1998) with postoperative anal fistula.

The diagnostic criteria for anal fistula refer to the guidelines for Clinical Diagnosis and Treatment of Anal Fistula (2006 Edition) jointly formulated by the Colorectal and Anal Surgery Group of Chinese Society of Surgery, Anorectal Branch of Chinese Society of Traditional Chinese Medicine, and Specialized Committee of Colorectal and Anal Diseases, Chinese Association of Modern Medicine.2. Aged 18 to 75.3. 4cm^2^ ≤ postoperative wound area<30 cm^2^.4. TCM syndrome differentiation is dampness–heat blood stasis syndrome, referring to the People’s Republic of China Industry Standard for Traditional Chinese Medicine Diagnosis and Efficacy Criteria for Anal Leakage Syndrome.5. No previous surgery for anorectal disease and no abnormal anal morphology or function.6. Voluntary participation and signed informed consent.

